## Abstract

**Background:**

Diminished ovarian reserve (DOR) is a condition in which the ovary loses its normal reproductive potential, compromising fertility. Although the prevalence and incidence of DOR is increasing, there are currently no effective treatments for this condition. Acupuncture has been reported as an alternative therapy for female infertility. The purpose of this study is to investigate the effect of acupuncture for women with DOR.

**Methods/design:**

In this randomized controlled trial, a total of 120 women with DOR will be randomly assigned to receive either acupuncture or sham acupuncture for 12 weeks. The primary outcome will be determined by the mean change from baseline in the antral follicle count (AFC) at week 12. Secondary outcomes include serum levels of FSH, LH, E2, and AMH, the length of menstrual cycle, and the score of Self-Rating Anxiety Scale (SAS).

**Discussion:**

This study is expected to investigate the effectiveness of acupuncture versus sham acupuncture in improving ovarian reserve for women with DOR.

**Trial registration:**

Acupuncture-Moxibustion Clinical Trial Registry ChiCTR1800014988. Registered on 6 February 2018

## Background

Decreased or diminished ovarian reserve (DOR) refers to women of reproductive age having regular menses whose response to ovarian stimulation is reduced in comparison to women of similar age [1]. Currently, there is no uniformly accepted definition of DOR. The term DOR may refer to three related but distinctly different outcomes: oocyte quality, oocyte quantity, and reproductive potential. Ten percent of women (totaling 275,000) in an infertility clinic of USA were diagnosed with DOR [2, 3]. Data from the US-based national Society for Assisted Reproductive Technology system showed 32% of in vitro fertilization (IVF) cycles (approximately 66,000 cycles) carried a diagnosis of DOR [4]. In China, the infertility rate of childbearing couples has increased from 3% 20 years ago to 15% at present [5]. Among them, infertility caused by DOR accounts for 10% of the total number of female infertility [6]. A significant upward trend in the prevalence of DOR was noted in patients up to 40 years of age [7, 8]. Without timely and effective interventions, women with DOR may experience ovarian atrophy within 1 to 6 years, and their disease progress to primary ovarian insufficiency (POI) simultaneously [9].

At present, few modalities are available for the treatment of DOR. The commonly used hormone replacement therapy (HRT) [10] is mainly prescribed for women with DOR without birth demand. HRT is effective for relieving low estrogen symptoms but with a high recurrence rate after drug discontinuation and does not improve ovarian function. An international survey [11] indicated DOR patients respond poorly to controlled ovarian stimulation (COS) resulting in retrieval of fewer oocytes, producing poorer quality embryos, and reduced implantation rates and pregnancy rates. Some studies suggested the addition of growth hormone [12] during ovarian stimulation could enhance the response of granulosa cells to gonadotropins and dehydroepiandrosterone [13] could improve ovarian function. However, there is insufficient evidence to support their correlation. Thus, effective treatment methods for DOR are still needed to improve female reproductive health and their quality of life.

Acupuncture has been used for the treatment of female infertility for thousands of years in China. A prospective observational study [14] reported significant decrease of follicle-stimulating hormone (FSH) and luteinizing hormone (LH) levels and increase of estradiol (E2) level among DOR patients treated with acupuncture. Similar results were observed in randomized controlled trials (RCTs) for women with POI [15], a condition showing a more serious decline of ovarian function than DOR. In recent years, acupuncture has gained worldwide popularity as an adjunct to assisted reproductive technology. A higher clinical pregnancy rate was reported in patients receiving acupuncture prior to and post-embryo transfer during IVF-ET cycles [16, 17]. In this trial, a prospective randomized sham-controlled study will be conducted to investigate the effect of acupuncture for women with DOR.

## Study design and methods

### Study design

This is a prospective, single-center, randomized, sham-controlled trial. Participants will be assigned to receive acupuncture or sham acupuncture in a 1:1 ratio. This study is in accordance with the principles of the Declaration of Helsinki and has been approved by the ethics committee of the Institute of Acupuncture and Moxibustion, China Academy of Chinese Medical Sciences (CACMS) (approval number: SC2017-12-22-1-1). Written informed consent will be obtained from each participant before enrolment.

Total observation period will be 32 weeks, including an 8-week screening period (weeks − 8–0), a 12-week intervention period (weeks 0–12), and a 12-week follow-up period (weeks 13–24). Assessments will be conducted at baseline, week 12, and week 24. Flowchart and study design schedule are presented in Fig. 1 and Table 1, respectively.

**Fig. 1 Fig1:**
[figure not shown]
Trial flow chart

**Table 1 Tab1:** Study schedule of enrolment, intervention, and assessments

Time point	Screening period (data collection)	Intervention period		Follow-up period
	Weeks − 8 to 0	Week 1–week 11	Week12	Week 24
Enrolment				
Informed consent	×			
Eligibility screen	×			
Randomization	×			
Allocation	×			
Interventions				
Acupuncture group		×	×	
Control group		×	×	
Assessments				
AFC	×		×	×
Serum levels of FSH, LH, and E2	×		×	×
AMH	×		×	×
Length of menstrual cycle	×		×	×
SAS score	×		×	×
Safety				
Adverse events	×	×	×	×

*AFC* antral follicle count, *AMH* anti-Müllerian hormone, *FSH* follicle stimulating hormone, *LH* luteinizing hormone, *E2* estradiol, *SAS* Self-Rating Anxiety Scale

### Participants

A total of 120 patients with DOR will be recruited from outpatients of acupuncture and moxibustion hospital of CACMS via hospital poster, WeChat (a free popular social application in China) or network advertisement. Two staff members who are responsible for participant recruitment will conduct the consenting process in a separate clinic room in our hospital. Participants will be informed of details of the study which includes but is not limited to the objectives, interventions, potential benefits, and risks. Should the participants agree to join the study, they are required to submit a signed informed consent form.

### Inclusion criteria

Participants who meet the following inclusion criteria will be included: (1) female, aged 18–40 years; (2) meet any of the following three items in both tests with an interval of at least 4 weeks: (a) 10 IU/L < FSH < 20 IU/L, tested on days 2–4 of menstrual cycle; (b) anti-Müllerian hormone (AMH) < 1.1 ng/mL; (c) antral follicle count (AFC) < 5–7, tested on days 2–4 of menstrual cycle; and (4) voluntarily join the research and sign the informed consent.

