### Randomization and blinding

This trial will use the central randomization system provided by the Institute of Basic Research in Clinical Medicine of CACMS. Eligible participants will be randomly assigned to acupuncture or control groups in a 1:1 ratio. The randomization scheme and its related parameters protected by a strict viewing permission will be kept as blind code by a member of staff who is not involved in this study. The allocation sequence will be computer-generated. Acupuncturists will be responsible for randomization. They will obtain a random number and group assignment after entering gender and birthday of eligible participants into the central randomization system over cellphone or web. Participants, outcome assessors, and statisticians will be blind to treatment allocation during the whole study. Acupuncturists will not take part in the outcome assessment. Emergency unblinding is generally not required when serious adverse event (SAE) occurs. Unblinding during the trial will be permissible when acupuncture may affect the choice of treatment for SAE.

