### Measurements

#### Outcome measures

The primary outcome is the change of AFC from baseline to week 12. The differences between groups will be assessed. AFC is the number of visible ovarian follicles with a mean diameter of 2–10 mm observed during transvaginal ultrasound performed on menstrual cycle days 2–5. The number of antral follicles correlates with quantity of remaining follicles and with the ovarian response during COS. A low AFC is associated with poor response to ovarian stimulation during IVF.

Secondary outcomes are listed as follows.

(1) The mean change from the baseline in serum basal FSH, LH, and E2 will be compared between groups at week 12 and week 24.

Basal serum levels of FSH, LH, and E2 are measured on days 2–4 of the menstrual cycle. Basal FSH is commonly used to assess ovarian reserve, and high values greater than 10 IU/L are related with DOR and poor response to ovarian stimulation. An elevated basal estradiol level (greater than 50 pg/ml) in the early follicular phase indicates reproductive aging and hastened oocyte development.

(2) The mean change from baseline in serum AMH will be compared between groups at week 12 and week 24.

AMH is produced by the granulosa cells of primary, preantral, and antral follicles of 2–6 mm in diameter. It is a good predictor of oocyte quantity. A decrease of AMH indicates oocyte depletion. Since the level of AMH is fairly stable within and between menstrual cycles, it can be measured on any day of the cycle.

(3) The mean change from baseline in AFC at week 24 will be compared between groups.

(4) Change in the length of menstrual cycle at weeks 12 and 24. The length of menstrual cycle is divided into 3 categories: normal, antedated, or delayed menorrhea. The proportion of each category will be compared between groups at weeks 12 and 24.

(5) The mean change from baseline in the score of Self-Rating Anxiety Scale (SAS) will be compared between groups at weeks 12 and 24.

SAS is a self-rating scale for measuring the presence and severity of anxiety [20]. It consists of 20 items with 4 possible responses: (1) never, (2) rarely/sometimes, (3) frequently, and (4) always. The standard score is the integer part of the raw score (the sum of the 20 items) multiplied by 1.25. A higher score denotes more serious anxiety symptoms. In this trial, we will use a validated Chinese version of SAS [21].

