## Discussion

This trial is to reveal whether acupuncture is effective in improving ovarian reserve for women with DOR. Though observational studies [23] showed promising hormone changes and improvement of TCM symptoms, RCTs focusing on women of DOR is scarce. Available RCTs on DOR are limited by small sample sizes, heterogeneity among acupuncture protocols and control methods (usually drug control or wait list), and single ovarian reserve tests (usually sex hormones) [24, 25]. In this trial, we will use superficial acupuncture as sham control. Although placebo is a better control to investigate the effect of acupuncture than superficial acupuncture, it is hard to conduct owing to the high recognition of acupuncture by patients in China and the complexity of acupuncture protocol in this trial. Given patients’ strong desire and urgent need for treatment, superficial acupuncture seems to be a better control method than placebo or wait list; nevertheless, its effect cannot be ignored.

In assessment of ovarian reserve, basal levels of FSH, LH, and E2 are the most commonly used outcomes for DOR. According to the committee opinion of the American Society for Reproductive Medicine, there is emerging evidence to support the use of AMH and AFC as a screening test for poor ovarian response [26]. AMH, produced by granulosa cells of early follicles, reflects the size of the primordial oocyte pool. It is gonadotropin-independent and thus remains relatively consistent within and between menstrual cycles. AFC correlates with both number of remaining follicles and ovarian response during COS. Compared with basal serum levels of FSH, LH, and E2, AMH and AFC are more significant predictors of poor ovarian response. Since no single measure of ovarian reserve has 100% sensitivity and specificity to detect DOR, biochemical and imaging measures (including FSH, LH and E2, AMH, and AFC) will be combined in this trial to assess the change of ovarian reserve.

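### Entry on FSH or AMH alone leaves baseline AFC unrestricted, yet the stated comparison for AFC change, the primary outcome, does not adjust for baseline AFC

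*Protocol article*

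**What the plan says.** Protocol article, Inclusion criteria: participants must "meet any of the following three items in both tests with an interval of at least 4 weeks". The three items are "10 IU/L < FSH < 20 IU/L, tested on days 2–4 of menstrual cycle", "anti-Müllerian hormone (AMH) < 1.1 ng/mL" and "antral follicle count (AFC) < 5–7, tested on days 2–4 of menstrual cycle". One is enough. The Exclusion criteria set no upper limit on AFC.

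Outcome measures: "The primary outcome is the change of AFC from baseline to week 12". Table 1 places an AFC measurement in the screening period, at week 12 and at week 24, so every participant should have a baseline count.

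Statistical analysis: continuous outcomes are compared between groups by an independent t test or a non-parametric test, on all randomised women. No baseline covariate is named.

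Sample size: a mean AFC gain of 2.25 under acupuncture, 0.8 assumed under sham, SD 2.22, 90% power, two-sided 5%, hence 50 per group and 120 in total after the dropout allowance.

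**The concern.** The entry rule widens the spread of the variable on which the primary outcome is built. Some women qualify because their AFC is low on two tests. Others qualify on a hormone level and may have a count well above the range in the AFC item. For example, a woman with FSH of 11 IU/L on both tests and an AFC of 14 is eligible.

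Change from baseline usually depends on the baseline value: low counts tend to rise on remeasurement and high counts to fall. Where that holds, an unadjusted comparison of change carries variation that the baseline count could remove. A chance difference in baseline AFC between arms also passes into the treatment estimate.

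There is a question of interpretation too. A single mean difference does not show whether a gain occurred in women whose count was low at entry, in the others, or in both.

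**Working it through.** **1. The plan's own figure.** Difference δ = 2.25 − 0.8 = 1.45. SD σ = 2.22, which I take to be the SD of the change, since it is used with mean changes.

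n per group = 2 × [σ(1.960 + 1.282)/δ]² = 49.26, rounded up to 50. The plan's figure reproduces. The t-test solution is 50.24. At 50 per group the standard error is 2.22 × √(2/50) = 0.444, the noncentrality is 1.45/0.444 = 3.27, and power by noncentral t (98 df) is 89.9%.

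**2. What adjustment would gain.** Let r be the within-group correlation between baseline AFC and its change. ANCOVA replaces σ by σ√(1 − r²) and uses one more degree of freedom. The treatment estimate is the same whether the outcome is week-12 AFC or its change, once baseline is in the model. The article gives no r, so the values below are assumptions.

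| \|r\| | Residual SD | Standard error | Noncentrality | Power, 50 per group |
|---|---|---|---|---|
| 0 (unadjusted) | 2.220 | 0.444 | 3.27 | 89.9% |
| 0.3 | 2.22 × √0.91 = 2.118 | 0.424 | 3.42 | 92.4% |
| 0.5 | 2.22 × √0.75 = 1.923 | 0.385 | 3.77 | 96.2% |

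**3. Chance imbalance.** Assume simple 1:1 randomisation with 60 per group. The standardised baseline difference then has standard error √(2/60) = 0.183. The chance that it exceeds 0.2 SD in either direction is 2 × [1 − Φ(0.2/0.183)], about 27%. For 0.3 SD it is about 10%.

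An imbalance of k SD shifts the unadjusted difference in change by k × |r| × 2.22. For k = 0.2 this is 0.2 × 0.3 × 2.22 = 0.13 follicles, or 0.2 × 0.5 × 2.22 = 0.22. Against a planned difference of 1.45 that is 9% or 15%. ANCOVA removes this shift as far as the relation is linear.

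**4. Cost in precision of a low-AFC estimate.** The share of women who will meet the AFC item is not given. If half did (25 per group, SD 2.22), the 95% half-width would be 2.011 × 2.22 × √(2/25) = 1.26. For all women at 50 per group it is 1.984 × 0.444 = 0.88, both unadjusted.

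**The case against.** **The entry rule is defensible.** The Background says that DOR has no uniformly accepted definition, and the Discussion says that no single marker is fully sensitive and specific. By the protocol's own definition, a woman who qualifies on FSH or AMH has DOR, and the stated aim is to improve ovarian reserve, not to restore a normal count. The Discussion's remark that "AMH and AFC are more significant predictors of poor ovarian response" compares these two with basal FSH, LH and E2. It could be held against entry on FSH alone, but not against entry on AMH. This objection stands, and eligibility should stay as it is.

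**Covariates may be in an analysis plan that is not shown.** This stands in part. The article does more than stay silent, however: it names the between-group test, and that test is unadjusted. If an analysis plan already specifies ANCOVA, the two texts should be aligned.

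**A reader might infer that gender, constant in a trial of participants who are "female, aged 18–40 years", takes the place of AFC as a randomisation factor.** The article says only that assignment is obtained "after entering gender and birthday of eligible participants into the central randomization system". It does not call either entry a stratification factor; they may be identifiers, and birthday does vary. The scheme's parameters are kept under restricted access, so the article does not show whether strata exist. Unstratified randomisation would in any case be valid.

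**A reader might also infer a large loss of power.** If 20%, 30% or 40% of entrants had no gain over sham, the difference would be 1.45 × 0.8 = 1.16, 1.45 × 0.7 = 1.015 or 1.45 × 0.6 = 0.87, and power at 50 per group 73.5%, 61.9% or 49.2%. The arithmetic is correct, but the documents give neither these shares nor a reason to expect no effect. Women with higher counts might gain as much or more. The gain of 2.25 comes from the team's earlier DOR study, whose entry criteria are not shown; if its mix was similar, any dilution is already in the planning figures. Nor would stratification restore a diluted mean.

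**Conclusion.** The point holds as a modest, specific improvement to the primary analysis. Baseline AFC is unrestricted for women entering on FSH or AMH, AFC change is primary, and the stated comparison ignores a baseline value that the trial already records.

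The unadjusted test is not invalid and the sample size is not shown to be wrong. The expected benefit is a power gain of about 2 to 6 percentage points, together with protection against chance imbalance. It rests on an assumed correlation of 0.3 to 0.5 in absolute value between baseline and change. With no correlation there would be essentially no gain, at the price of one degree of freedom.

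The documents do not establish a fault in randomisation, a fault in eligibility or a quantified loss of power.

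**What to change.** Keep eligibility and allocation unchanged.

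1. **Primary comparison.** In Statistical analysis, specify an ANCOVA of week-12 AFC (or its change) on treatment with baseline AFC as a continuous covariate, and report the adjusted difference with its 95% interval. If more than one screening count exists, state which one is the baseline.
2. **Supportive analysis.** Report the treatment effect by baseline AFC, through a treatment-by-baseline-AFC interaction. The alternative is an estimate in women who met the AFC criterion at entry, which first requires the investigators to settle the range in "antral follicle count (AFC) < 5–7, tested on days 2–4 of menstrual cycle" as one cut-off for this analysis. The interaction needs no cut-off.
3. **Timing.** Record both changes before any unblinded look at outcomes. Recruitment had begun and data collection was in progress when the article was written. Since only the analysis changes, women already randomised are covered equally.

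Cost: two sentences of analysis text, with no extra patients, visits or measurements. The downside is that the supportive estimate has a wider interval than the overall one and should not be read as a confirmatory test.

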### Statistical considerations

#### Sample size

The results of our previous study on acupuncture for DOR [22] showed that the increase in mean AFC from baseline to week 12 was 2.25 in acupuncture group and 0.30 in the wait list control. Based on these results, we assumed an increase of 0.8 in AFC for sham acupuncture after 12-week treatment. A sample size of 50 participants per group will be needed to provide 90% power and a two-sided significance level of 5%, assuming a standard deviation of 2.22. Allowing for a 20% dropout rate, 120 participants will be recruited with 60 participants per group.

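### Baseline AFC is not defined although screening can yield two values; averaging the available values and adjusting for them would be a nearly free gain in precision over the unadjusted comparison

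*Protocol article*

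**What the plan says.** - **Inclusion criteria:** participants must "meet any of the following three items in both tests with an interval of at least 4 weeks". The three items are FSH, AMH and AFC, and any one suffices. The AFC item reads "antral follicle count (AFC) < 5–7, tested on days 2–4 of menstrual cycle".
- **Outcome measures:** "The primary outcome is the change of AFC from baseline to week 12". AFC is defined there once, by "transvaginal ultrasound performed on menstrual cycle days 2–5".
- **Study design:** "Assessments will be conducted at baseline, week 12, and week 24". Table 1 has a single pre-treatment AFC column, covering the whole 8-week screening period, which is long enough for both screening tests.
- **Statistical analysis:** continuous outcomes are compared between groups by an independent t test or a non-parametric test. No baseline covariate is named.
- **Sample size:** the mean AFC increase in the earlier study "was 2.25 in acupuncture group and 0.30 in the wait list control". The sham increase is assumed to be 0.8 and the SD 2.22, which gives 50 per group for 90% power at two-sided 5%. Recruitment is 60 per group to allow for 20% dropout.

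**The concern.** The eligibility rule can produce two pre-treatment AFC values at least four weeks apart. The primary endpoint then rests on a baseline that could be the first scan, the last, the lower, the mean or a separate scan. If one scan is used, an unadjusted change score carries the full within-woman variation of that scan into every participant's result, while a second value already collected goes unused.

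The AFC windows also differ. If an eligibility scan (days 2–4) serves as baseline, the two ends of the change score are measured under slightly different timing rules.

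What is at stake is precision on the primary endpoint and a baseline rule fixed before unblinding.

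**Working it through.** **1. Reproduce the plan's figure.** The difference is 2.25 − 0.8 = 1.45, with SD 2.22. The normal-approximation formula n = 2(1.96 + 1.2816)² × 2.22² / 1.45² gives 50 per group after rounding up (power 90.4%), as stated. With the exact t test, power at 50 per group is 89.9%. Recruiting 60 per group and losing 20% leaves 60 × 0.8 = 48 per group, where exact t power is 88.6%. This is the reference value below.

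**2. Averaging two baselines in the change score.** Let s² be the variance of one AFC, r the correlation of a baseline AFC with week-12 AFC, and b the correlation between the two baselines.
- One baseline: Var(change) = 2s²(1 − r).
- Mean of two: Var(change) = s²[1 + (1 + b)/2 − 2r].
- If b = r, the second expression equals 1.5s²(1 − r), so the ratio is 0.75 for any r.

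The SD becomes 2.22 × √0.75 = 1.92. If instead half of the single-baseline change variance is true between-woman variation in change, only the other half shrinks: 0.5 + 0.5 × 0.75 = 0.875, and the SD is 2.22 × √0.875 = 2.08.

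| Assumption (two scans in every woman) | Variance ratio | SD | Exact t power, 48 per group |
|---|---|---|---|
| One baseline | 1.00 | 2.22 | 88.6% |
| Mean of two, half the variance true change | 0.875 | 2.08 | 92.3% |
| Mean of two, b = r | 0.75 | 1.92 | 95.5% |

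If the two baselines correlate more with each other than with week 12 (b exceeds r by 0.1 to 0.2, for r = 0.3, 0.5 and 0.7), the ratio runs from 0.786 to 0.917 and power from 94.7% down to 91.1%.

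**3. The same comparison within ANCOVA.** With all pairwise correlations equal to r:
- One baseline as covariate: residual variance s²(1 − r²).
- Mean of two as covariate: s²[1 − 2r²/(1 + r)].
- Ratio of the second to the first: (1 + 2r)/(1 + r)².

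At r = 0.5 this is 2/2.25 = 0.89, and at r = 0.8 it is 2.6/3.24 = 0.80. A second baseline therefore cuts the ANCOVA residual variance by about 11% to 20%. This is the gain from averaging once ANCOVA is in use. It takes the place of the 25% in step 2 and must not be added to it.

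**4. Both changes against the single-baseline change score.** The ratio is (1 + 2r)/[2(1 + r)], which is 2/3 = 0.67 at r = 0.5 and 2.6/3.6 = 0.72 at r = 0.8. The SDs are 1.81 and 1.89.

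**5. Cycle-day windows.** Days 2–4 lie inside days 2–5, so the difference is one permitted day. The article gives nothing from which its effect on the SD could be computed.

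**The case against.** **Missing detail.** Which pre-treatment value counts as baseline is commonly settled in the full protocol or the analysis plan, neither of which is shown. That stands: the absence of a definition is not in itself an error in the article. What remains is that the article does name its between-group test, and a clearly better use of data already being collected exists.

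**A single scan on a different day.** A reader might infer that the trial uses one baseline scan, taken in a different window from the outcome scan, and so wastes precision. The article does not say this. It never states that one scan is used. The days 2–5 definition is general and can cover baseline as well as week 12. The windows conflict within a change score only if an eligibility scan serves as baseline.

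**Two scans are not assured.** A woman may qualify twice on FSH or AMH, so the power figures, which give every woman two AFC values, overstate what the trial would gain.

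**A valid plan already.** A single pre-treatment baseline is conventional and unbiased under randomisation, and the stated 50 per group reproduces. This is correct: the point concerns efficiency, not validity.

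**Choice after seeing the data.** Participants, outcome assessors and statisticians are to be blind throughout, and both candidate values precede randomisation. This limits the scope for picking a favourable baseline, so little weight should rest on that risk.

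**Conclusion.** The point holds as an improvement in method. Where two screening AFC values exist, their mean is a better baseline than either one alone, and adjusting for it is better than an unadjusted comparison of changes.

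The size depends on assumptions. With two scans in every woman and equal pairwise correlations, averaging lowers the change-score variance by 25% and raises power at 48 per group from 88.6% to 95.5%, or to 92.3% if half the variance is true change. Treat these as upper bounds: the article reports no correlations and does not ensure two scans. Within ANCOVA the gain from the second baseline is about 11% to 20% of residual variance for correlations of 0.5 to 0.8.

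The window difference is a wording inconsistency to reconcile. It applies equally to both arms, so it can add noise but cannot bias the comparison between them.

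**What to change.** Before unblinding, make these changes:

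1. Define baseline AFC, and likewise baseline FSH, LH, E2 and AMH, as the mean of all pre-randomisation screening values, or the single value where only one exists.
2. Make the primary analysis an ANCOVA of week-12 AFC on treatment group with that baseline as covariate. The treatment effect is the same as from an ANCOVA of the change score with the same covariate, so the endpoint can still be described as change from baseline.
3. Reconcile the AFC cycle-day windows in Inclusion criteria and Outcome measures, and state which window applies to the baseline, week-12 and week-24 scans.

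The first two cost a sentence each and need no extra scan. The small downside is a noisier baseline in women with only one AFC, which reduces the gain without biasing the randomised comparison. For the third, the Trial status section says data collection is in progress. Scans already done cannot be re-timed, so the reconciled wording should also say how they are handled.
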